Randomization is stratified by sex in blocks of equal size, allowing us to investigate sex as an effect-modifying biological variable. To control response fatigue, we created 6 different permutations of the baseline survey, each with a different order of instruments, which are also balanced within blocks. The research assistants responsible for arm allocation are blinded to block size to prevent contamination.

After randomization, all study materials, including any equipment and/or materials, are distributed to the participants according to the treatment arm. Medication titration occurs again at week 8, and at subsequent follow-up visits at weeks 13, 26, 39, and 52 to ensure optimal treatment. Data collection follow-up visits take place at weeks 13, 26, 39, and 52, where a consistent set of study measures is collected—BP, health status, weight, adherence to BP measurements, physical activity, sodium intake, and medication adherence self-monitoring. Technology acceptance measures, including perceived ease of use and perceived usefulness, are also collected.

For medication titration and follow-up visits, patients are instructed to bring their HTN medications with them so pill counts can be conducted. Pill counts are used to avoid prescribing potentially harmful up-titration in antihypertensive therapy for patients with elevated BP at follow-up visits that may be because of medication noncompliance. For patients who self-report not filling prescriptions between visits, or when the expected number of pills found in the participant’s medication bottles (based on dosage and dispense date) suggests a less than 80% medication adherence, we continue with the same regimen without adjustment. We also monitor for any potentially harmful renal or metabolic issues at weeks 0, 26, and 52 and adjust medications accordingly. In addition to the medications, participants are instructed to bring study-dispensed devices so data can be downloaded, and adherence to self-monitoring behaviors can be ascertained.

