### Statistical Analysis Plan

#### Analysis of Blood Pressure Control

To determine the effect of MI-BP on BP at 1 year (aim 1) and to determine whether BP control is better in intervention-group participants compared with controls (hypotheses 1a), we will conduct a comparative analysis using a logistic regression with BP control as the outcome and study arm as the primary factor, controlling for demographic characteristics such as age, gender, medical history, baseline levels of functional status, health literacy, HTN knowledge, self-efficacy, and baseline BP at randomization. To determine whether mean SBP is better in the intervention group, compared with controls (hypothesis 1b), differential reduction in the coprimary outcome of SBP will be assessed in a linear mixed-effects regression framework, with time (baseline and end-of-trial), group, and time-by-group interaction as the primary independent variables. The subject-level characteristics used in the analysis of the primary outcome will be controlled in the regression model.

To determine the effect of MI-BP on secondary outcomes (aim 2), we will also use linear mixed-effects regression models with the secondary outcomes of interest as the dependent variables and week (as a continuous variable), study group, and week-by-group interaction as the primary independent variables. All appropriate model diagnostics will be carried out.

During data analysis, we will statistically address missing data resulting from incomplete data collection or participant attrition using the multiple imputation technique. Missing values will be imputed by repeatedly and iteratively fitting a sequence of regression models; it is a technique that is flexible in allowing different types of variables (categorical and continuous) to be imputed together without requiring any multivariate joint distributional assumption. Missing values are sequentially updated using bootstrap or Markov Chain Monte Carlo based on multiple regression models with other variables as covariates. This procedure will be conducted for 10 repetitions or cycles, a number considered adequate for most applications, thereby constructing an *imputed* dataset. Results from the 10 regressions will be combined with the imputed data using Rubin’s formula [39].

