For the long-term cost-effectiveness analysis, we will create a mathematical model of long-term quality of life and mortality because of HTN, which will be based upon other models in the literature, such as the approach used by Smith-Spangler et al [43], which modeled the relationship between SBP and long-term heart attack and stroke using a logistic risk function based on the Framingham data. Costs of disease states such as heart attacks and strokes will be taken from extant literature and databases such as the Medical Expenditure Panel Survey and Healthcare Cost and Utilization Project of the Agency for Healthcare Research and Quality. Health utilities will be taken both from the utilities collected and the medical literature (particularly for heart attacks and strokes). The models will begin with the health state of the participants at the end of the trial and will model health outcomes into the future. We will explore various assumptions about the durability of BP changes (eg, continuing improvement, stable BP, regression to prestudy BP levels). These cost-effectiveness analyses will follow standard guidelines for a *reference case* analysis, while the modeling approach and analysis will follow recent guidelines [44-46].

In addition to analyses for our stated aims, we also intend to conduct analyses to look at the patterns of MI-BP use that are associated with improved outcomes. For each of our self-monitoring behaviors (BP, physical activity, sodium intake, and medication adherence), we will calculate an overall utilization rate by dividing the number of logged data points by the total number of expected data points. Adherence to behavioral self-monitoring uptake for each activity will be compared within the MI-BP arm by means of count regression with the number of adherence instances (among the repeated observations) as outcome. Models will be controlled for variables similar to those in aim 1. To investigate whether better adherence to the self-monitoring uptake corresponds to an improvement in BP, we shall use a mixed-model analysis similar to that in aim 1 with BP measure as outcome and adherence as time-dependent binary covariates. Different self-monitoring behavioral components will simultaneously be used in the same model.

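### The adherence-to-BP model does not separate within-person association from stable differences between participants, and the reference to aim 1 does not settle what it tests

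*Protocol article*

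**What the plan says.** The last paragraph under Analysis of Cost-Effectiveness Data describes exploratory work on patterns of app use. Its question is framed as change: "To investigate whether better adherence to the self-monitoring uptake corresponds to an improvement in BP". The model is then given: "we shall use a mixed-model analysis similar to that in aim 1 with BP measure as outcome and adherence as time-dependent binary covariates". There is one adherence covariate per behaviour, and they enter jointly: "Different self-monitoring behavioral components will simultaneously be used in the same model". Just before this, the section states "Models will be controlled for variables similar to those in aim 1".

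The aim 1 mixed model, under Analysis of Blood Pressure Control, is a "linear mixed-effects regression framework, with time (baseline and end-of-trial), group, and time-by-group interaction as the primary independent variables". The aim 1 covariates include demographic and clinical characteristics, health literacy, hypertension knowledge, "self-efficacy, and baseline BP at randomization".

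Procedures fixes when logging can begin: "After randomization, all study materials, including any equipment and/or materials, are distributed to the participants according to the treatment arm". Baseline is week 0 and randomisation is at week 2.

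The article does not say whether adherence enters as a main effect only or also in an interaction with time. It mentions no split into within-person and between-person parts.

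**The concern.** The question is about improvement, but the outcome is a level. In a random-intercept model, the coefficient of a time-varying covariate is a weighted mix of two associations. One compares a participant's adherent visits with the same participant's other visits. With time in the model, that is a fair form of the question. The other compares people who usually log with people who usually do not. Adherence is not randomised, so the second can differ from zero although no one's BP responds to logging.

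At stake is the reading of the usage results. A significant coefficient could be taken to show that self-monitoring goes with falling BP when regular loggers simply had lower BP throughout. If regular loggers had higher BP, a real benefit could be hidden.

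**Working it through.** **Inputs from the protocol.** Sample Size: 161 completers per arm, SD 10 mmHg, intra-subject correlation 0.5, 17-point fall in the MI-BP arm. Procedures: follow-up measurements at weeks 13, 26, 39 and 52.

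**Assumed, not in the protocol.** A correlation c of 0, -0.3 or -0.5 between a participant's logging tendency and stable SBP; about half of visits adherent; one behaviour only; baseline SBP as the only covariate.

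**Step 0: the plan's own figures.** For 30% against 47.5% (mean 38.75%), n = [1.960 x sqrt(2 x 0.3875 x 0.6125) + 1.282 x sqrt(0.30 x 0.70 + 0.475 x 0.525)]^2 / 0.175^2 = (1.350 + 0.869)^2 / 0.030625 = 160.8, so 161 per arm is reproduced. With 19% attrition, 161 / 0.81 = 198.8, which is the stated 198 apart from rounding. The plan gives no error rate or power for the adherence analysis.

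**Step 1: what one baseline reading can remove.** Stable variance is 0.5 x 10^2 = 50, and visit-to-visit variance is also 50. The slope of the stable level on one baseline reading is 50 / (50 + 50) = 0.5. A stable gap g between loggers and non-loggers is therefore reduced by about 0.5g, leaving about 0.5g. The unexplained stable variance is 50 - 50^2 / 100 = 25.

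**Step 2: simulation with no adherence effect.** SBP = 150 + u + e - 17 x (week / 52), with u and e each of variance 50, so everyone falls alike. A visit is adherent when tendency plus standard normal noise exceeds 0, and the tendency has correlation c with u. Random-intercept fits, n = 161, 600 runs, two-sided 5% test:

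| Test | c = 0 | c = -0.3 | c = -0.5 |
|---|---|---|---|
| Main effect, follow-up visits | 5.2% | 19.7% | 49.2% |
| Main effect + baseline SBP covariate | 4.7% | 13.3% | 34.2% |
| Main effect, baseline visit kept as outcome row | 4.8% | 13.2% | 33.2% |
| Time-by-adherence, follow-up visits | 4.7% | 5.2% | 4.7% |
| Within-person deviation term | 4.0% | 6.0% | 5.0% |

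The mean spurious coefficient in the second row is -0.58 mmHg at c = -0.3 and -1.05 mmHg at c = -0.5. The simulation standard error is sqrt(0.133 x 0.867 / 600) = 1.4 points at 13.3% and sqrt(0.342 x 0.658 / 600) = 1.9 points at 34.2%. Repeat simulations on the same protocol figures gave 13-16% and 33-34%.

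**Step 3: does the reference to aim 1 settle it?**

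*Baseline and week-52 rows.* App and devices arrive after randomisation, so time-dependent app adherence is 0 for everyone at baseline. Time x adherence is then the same column as adherence: of the four columns (intercept, time, adherence, interaction) only three are independent. Without further covariates, the remaining coefficient is the week-52 gap minus 0.5 times the baseline gap, so a constant gap g returns (1 - 0.5)g. Assumed gaps of 2, 3 and 5 mmHg give 1.0, 1.5 and 2.5 mmHg with no change in anyone.

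*Follow-up rows.* The interaction holds its 5% level but asks only whether the gap widens between weeks 13 and 52. With a true constant benefit of 3 mmHg in adherent periods, it detected the benefit in 4-6% of simulated trials, against 96-97% for the within-person term. Hand check of the latter: the correlation between two visits' adherence is (2 / pi) x arcsin(0.5) = 0.333; within-person variance is 0.25 x (1 - 0.333) = 0.167; SE = sqrt(50 / (161 x 3 x 0.167)) = 0.79 mmHg; 3 / 0.79 = 3.8; power is about 97%.

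*Fixed adherence group.* A two-row model with participants classed once as adherent or not, and a time-by-class term, rejects in 5.3%, 5.3% and 5.0%. It is sound in size, but the class already equals 1 at baseline, so it is not the time-dependent covariate that the plan names.

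**The case against.** The strongest reply is that the text does not specify a lone main effect. It refers to a model resembling aim 1, which has "with time (baseline and end-of-trial), group, and time-by-group interaction as the primary independent variables", and an interaction form keeps the 5% level. This stands in part: a reader might infer that the plan fixes a single main-effect term, and the document does not say so. But Step 3 shows that, with time-dependent adherence, the interaction either duplicates the main effect or addresses a narrower question.

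Second, the inflation rests on an assumed correlation. This stands. At zero correlation the test is correctly sized. A reader might infer that stable traits certainly make loggers look better, but nothing in the protocol establishes this. The home-monitoring instructions tell users with extreme readings to measure again, so participants with worse BP might log more. The simulations also leave out the other aim 1 covariates, several of which are plausible common causes of logging and BP.

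Third, the deviation term ignores participants whose adherence never changes, although consistent loggers who improve are relevant to the question. This stands, and is why both terms should be reported. Nor is it a fault that the model compares periods: that is its useful part.

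Fourth, a condensed article may leave such detail to a fuller plan. If the fuller plan has the split, the point is met. The article does, however, state the outcome, the covariate form and the reference model, and that combination does not by itself answer its question.

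**Conclusion.** The point holds in a limited form. As described, the analysis does not isolate the association between adherence and improvement. If adherence enters as a main effect, stable between-person differences contribute to each coefficient, and one baseline reading removes only about half of such a gap. With no true effect, rejection is about 5%, 13-16% and 33-34% for assumed correlations of 0, -0.3 and -0.5. These figures rest on the protocol's SD and correlation, 161 participants, one behaviour, about half of visits adherent, and no covariate other than baseline SBP. They show what could happen and do not predict this trial's error rate.

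A reader might go further and conclude that the trial's efficacy findings are at risk. They are not: this analysis is additional to the stated aims and worded as association, and the coprimary comparisons do not use it. Low priority.

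**What to change.** In the paragraph on patterns of app use, specify the following:

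- Fit the model to clinic SBP at weeks 13, 26, 39 and 52 in the MI-BP arm, with visit as a factor, baseline clinic SBP and the other aim 1 covariates.
- For each behaviour, enter two terms: the participant's mean adherence over visits and the visit-specific deviation from that mean.
- Report both. Treat the deviation term as the main evidence that adherence goes with better BP, and label the person-mean term a between-person association open to confounding.

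The cost is a wording change and one extra derived variable per behaviour, with no new data. The price is a wider confidence interval for the deviation term. Participants whose adherence never changes inform only the person-mean term.

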#### Home Blood Pressure Monitoring and Tracking

MI-BP allows users to revicew both 1- and 4-week graphs of BP readings, collected via study-issued home BP cuffs. In addition to graphs, numerical logs of 1- and 4-week BP data are also available for review (see Figure 1 for screenshots of the MI-BP app). BP data can be either digitally synced, or manually entered into the MI-BP app. Participants with arm circumferences of 23 to 45 cm, which represents the majority of users, will receive a Bluetooth-enabled digital BP monitor (A&D UA-651BLE) that can store up to 30 BP measurements. With a touch of a button, this cuff can automatically sync collected measurements with the MI-BP app. For the participants who have an arm circumference between 42 and 60 cm, we will provide an extra-large arm monitor (LifeSource A&D UA-789). These cuffs are not Bluetooth-enabled and require manual data entry.

Users are instructed to measure and sync (or manually enter) their BP to the MI-BP app, at home, for a minimum of at least 3 days per week; however, daily self-monitoring and syncing are encouraged. When taking BP at home, users are instructed to take 3 consecutive readings and adhere to the following guidelines:

Relieve yourself in the bathroom before taking BP, if needed.Keep arm at heart level by resting it on a table during monitoring.Sit in a chair with a back and with feet flat on the floor for at least 5 min before taking BP.Avoid tobacco, caffeine, or alcohol for 30 min before taking BP.Avoid taking BP right after exercise, when emotionally upset, or in pain.Avoid talking while taking BP.

In the event that a participant records a BP with systolic reading of greater than 180 mmHg or less than 100 mmHg, or a diastolic reading of greater than 110 mmHg, the MI-BP users are then instructed by the study staff at baseline, as well as by automated notifications within the app at the time of the elevated reading, to do the following:

Wait for 5 min and then check BP again.If the SBP is still above 180 mmHg or less than 100 mmHg, or if the diastolic BP is still above 110 mmHg for 3 days in a row, call the research staff.Report to the ED and follow up after with a call to the research staff if experiencing symptoms of dizziness, chest pain, severe headache, visual changes, or numbness or weakness in face or extremities.

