### Sample Size

On the basis of data from our previous studies, we estimate that 30% of usual-care participants will achieve BP control (BP<130/80 mmHg) by 1 year. We consider at least 17.5% higher control rates for the intervention arm to be clinically meaningful. On the basis of a 2-sided chi-square test of comparing 2 proportions at a 5% level of significance, the power for detecting the difference between MI-BP self-monitoring arm and usual care is 90%, with 161 participants per arm. Allowing for 19% attrition based on our previous work in similar patient populations, we plan to recruit 198 participants per arm, for a total of 396 participants. It is anticipated that at the end of trial, both groups will improve on average SBP. We estimate a 10- and 17- point drop in the usual care and MI-BP arms, respectively, at 1 year. Further, a constant between-subject SD of 10 mmHg is assumed, along with an intra-subject correlation of 0.5. With 161 subjects per arm, we can detect a group-by-time interaction with power >95% at 5% level of significance.

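### The app-use analysis enters self-monitoring adherence in the BP model as yes/no covariates with no stated cut-point, although the logs support a graded measure

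*Protocol article*

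**What the plan says.** The last paragraph under Analysis of Cost-Effectiveness Data opens: "In addition to analyses for our stated aims, we also intend to conduct analyses to look at the patterns of MI-BP use" that go with better outcomes. It then sets out three steps.

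- For each of four behaviours (home BP, physical activity, sodium, medication), "we will calculate an overall utilization rate by dividing the number of logged data points by the total number of expected data points". This is a graded quantity, described as overall, so it gives one value per person.
- Uptake is compared within the MI-BP arm by "count regression with the number of adherence instances (among the repeated observations) as outcome".
- To ask whether higher adherence goes with improved BP, a mixed model like that of aim 1 is fitted "with BP measure as outcome and adherence as time-dependent binary covariates". The paragraph adds: "Different self-monitoring behavioral components will simultaneously be used in the same model".

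The article gives no cut-point or scoring rule for the binary covariate in this model, no reason for using one, and no effect size, power or correlation for the analysis. On how much logging to expect, Home Blood Pressure Monitoring and Tracking asks users to measure "for a minimum of at least 3 days per week; however, daily self-monitoring and syncing are encouraged". The physical activity section asks them to wear the pedometer daily.

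**The concern.** The question asked is graded, and so are the data. From week 13 the data collection visits are 13 weeks apart. If the model uses clinic BP at those visits, one interval holds at least 13 × 3 = 39 requested home-BP days and 13 × 7 = 91 pedometer days. Each set becomes a single yes or no.

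Two things follow if BP falls steadily with use. First, the coefficient of an active behaviour is estimated from less information, so a real association is easier to miss. Second, a yes/no version of an active behaviour adjusts only partly for it. Some of its effect then passes to other behaviours that the same users tend to log. The second point matters because Comparison With Previous Work names poor understanding of which components work as a gap in earlier research, and this joint model is the planned analysis closest to that gap. A cut that is not fixed in advance also leaves room to choose it after seeing the data.

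**Working it through.** **The plan's own figures.** The article states no power for the app-use analysis. Its sample size, set out "On the basis of a 2-sided chi-square test of comparing 2 proportions at a 5% level of significance", does reproduce. With 30% against 47.5%, the pooled proportion is 0.3875, and n = [1.960·√(2·0.3875·0.6125) + 1.282·√(0.30·0.70 + 0.475·0.525)]² / 0.175² = (1.350 + 0.869)² / 0.0306 ≈ 161 per arm, with power 90.04%. For attrition, 161/0.81 = 198.8, against 198 stated. From the same section come the SD of 10 mmHg and the intra-subject correlation of 0.5. Everything else below is an assumption.

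**Step 1: one normal covariate, linear relation.** A split with a fraction p above the cut c keeps the share φ(c)²/[p(1−p)] of the information. At the median this is 0.3989²/0.25 = 0.637. Power after the split is Φ(δ·√share − 1.960), where δ = 1.960 + z(starting power). From 90%, δ = 3.242, so 3.242 × 0.798 − 1.960 = 0.626. Power is then 73.4%, a loss of 16.6 points.

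| Split | Information kept | Loss from 80% | Loss from 90% | Loss from 95% |
|---|---|---|---|---|
| 50/50 | 0.637 | 19.1 | 16.6 | 13.0 |
| 80/20 | 0.490 | 30.0 | 27.9 | 23.7 |
| 90/10 | 0.342 | 42.6 | 42.5 | 39.1 |
| 95/5 | 0.224 | 53.7 | 56.5 | 55.0 |

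The largest loss for a median split, over all starting powers, is 19.4 points.

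**Step 2: four behaviours jointly, one observation each.** This simulation has 161 people, one active behaviour correlated 0.3 with BP, and correlations of 0, 0.3 or 0.6 between behaviours. With a linear relation, the loss is about 10 to 48 points for normal covariates and 6 to 70 for U-shaped rates. The 70 is 92.7% falling to 23.2%, with a 90/10 split. If the true relation is a step at the cut, the binary form instead gains about 6 to 83 points.

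**Step 3: four behaviours jointly, repeated visits.** This simulation has 161 people, 4 visits, SD 10 and intra-subject correlation 0.5. One behaviour lowers SBP by 1.5 mmHg per SD of its rate and the other three do nothing. Rates follow Beta(2,2), Beta(1,1) or Beta(1,2), with correlations of 0.3 to 0.7 between behaviours. Results are pooled over two independent runs (1,000 and 600 replicates per setting). At correlation 0.5, power is 78-84% with continuous rates, 58-67% with a median split and 18-42% with a cut at 0.8. Over all settings the loss was 14 to 66 points in one run and 11 to 64 in the other. The 0.8 cut is severe for some of these margins: under Beta(1,2) it labels 0.2² = 4% adherent, and under Beta(2,2) about 10%.

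**Step 4: leakage.** In large samples with normal covariates, correlations of 0.3 to 0.7 and median or 80/20 splits, an inactive behaviour takes up 9% to 26% of the active one's coefficient. In the step 3 simulation, its false-positive rate is about 5-8% at 1.5 mmHg per SD. At 3 mmHg per SD it is 7-11%, 10-14% and 11-16% at correlations 0.3, 0.5 and 0.7, against 3-7% with continuous rates.

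**Step 5: do the two harms coincide?** Doubling the effect roughly doubles the noncentrality. A median-split power of 59% implies 1.960 + 0.228 = 2.19, which doubles to 4.38, so power is Φ(4.38 − 1.96) ≈ 99%. For a median split, therefore, the power loss has nearly gone by the effect size at which false positives become noticeable. With a 0.8 cut, 18% implies 1.960 − 0.915 = 1.045, which doubles to 2.09, giving Φ(0.13) ≈ 55%. There both harms remain.

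**The case against.** The strongest reply is that the binary covariate need not be a split of the utilization rate at all. That rate is overall, while the covariate is time-dependent, and the count regression speaks of adherence instances. An occasion-level yes/no score fits the text at least as well. A reader might infer that the plan computes a rate and then dichotomises it; the wording does not establish that. The point survives in a narrower form, because logging between two BP visits still becomes one yes or no per behaviour under either reading.

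The time grid is also not fixed. Aim 1 uses baseline and end of trial, clinic BP is taken at every visit, and home BP exists in this arm. The 39 and 91 days therefore apply only to quarterly clinic BP. With shorter occasions less would be collapsed.

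Binary scoring has some basis in the document. The instructions are minimum targets, and pill-count adherence is scored against a 20% margin. Whether meeting the instructed minimum goes with better BP is a legitimate question. But the pill-count rule concerns pills taken, not app logging, so it supplies no cut for this model, and the article claims no threshold.

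Sodium logging is adaptive: 3-day periods recur after 2 or 4 weeks depending on whether the goal was met. The denominator then depends on the participant's own behaviour. This stands, and the fix has to deal with it.

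Finally, this is an observational, within-arm analysis outside the three aims, with no hypothesis test or power attached. That also stands and limits the consequence.

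**Conclusion.** The point holds as a weakness of a supplementary analysis. The plan states binary adherence covariates with no cut-point or rationale, where a graded measure is available and better matches the question. The direction of the harm is secure if the relation with BP is graded: some power is lost, and there is some leakage between correlated behaviours.

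The size is not secure. A reader might infer from the simulations that the plan forfeits a definite amount of power, such as 14 to 66 points. The document does not support that. The cut, the distribution of use, the effect and the correlations are all assumed, and the upper end needs extreme splits. The defensible statement is a range of about 6 to 70 points under linear truth, at most about 19 for a median split of one normal covariate, and a reversal under a true threshold at the cut. Nor should serious false-positive inflation be read as general: it is about 5-8% at 1.5 mmHg per SD, and reaches 7-16% only at about 3 mmHg per SD.

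**What to change.** In the app-use paragraph, replace the binary specification with this: for each behaviour, the proportion of expected data points logged in the interval before each BP visit enters as a continuous time-dependent covariate, with all four in the same model. Define the sodium denominator as the logging days actually prompted in that interval. Check linearity with a simple spline, which would also help to show a threshold-like shape. Keep a binary version, with its cut fixed in advance, as a sensitivity or descriptive analysis.

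The change needs no new data or participants. It does have a cost. Interval proportions must be derived in addition to the overall rate. Sodium proportions will be coarse: over 13 weeks, 3-day periods about every 4 or every 2 weeks give roughly 3 × 3 = 9 to 6 × 3 = 18 prompted days. A slope is also slightly harder to present than a difference between adherent and non-adherent users.
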